**Discussion::**

To our knowledge, this study protocol is the first to test the effect between S-1 versus S-1 plus cisplatin concurrent intensity modulated radiation therapy in the treatment of esophageal squamous cell carcinoma. If the result will be the same effect and fewer side effects and less costly in S-1 plus radiotherapy. It will supply more treatment selection for esophageal squamous cell carcinoma.

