Therefore, we designed a prospective, randomized, multicenter phase II trial to compare the efficacy and toxicity of combining S-1 or S-1 plus cisplatin with intensity modulated radiation therapy for esophageal squamous cell carcinoma.

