### Statistical analysis and randomization

3.6

At a bilateral test 0.05 significance level and a power of 85%, with a dropout rate for each group of 10%, observe 40% endoscopic CR, and to exclude a lower limit of confidence interval (CI) of 20% CR, the study requires a total of 88 samples. Randomization will be administered centrally by the SPSS. Patients who meet the inclusion criteria will be randomized on a 1:1 basis to one of the 2 groups.

The proportion of patients with a clinical response and their 95% confidence intervals will be calculated and reported. The number and proportion of specific cases will be analyzed. The Chi-square test and Kaplan–Meier method will be used to analyze the rates and severity of disease progression and overall survival rate, respectively, according to NCI-CTCAE (version 4), and a Fisher exact (probability) test will be used to analyze the correlations between clinical outcomes and toxicity.

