## Discussion

4

CRT has been accepted nowadays as the standard nonsurgical treatment for locally advanced EC.^[24]^ For 2 decades, chemotherapy, especially the 2-drug combination of cisplatin plus fluorouracil has been regarded as a standard regimen to treat patients with EC with distant metastases or recurrence.^[25]^ However, some retrospective studies have suggested that for patients with EC receiving radiotherapy combined with 2-drug chemotherapy have the severe toxicity.^[7,13–17]^ Our retrospective analysis of 133 cases of esophageal squamous cell carcinoma with complete statistical data found that for both OS and PFS, there was no significant difference between single and 2-drug chemotherapy combined with synchronous radiotherapy (unpublished). So we design this experiment to compare the complete remission rate of S-1 and S-1 combined with cisplatin in the treatment of esophageal squamous cell carcinoma.

*Expectations*: Compare S-1 plus cisplatin concurrent intensity-modulated radiotherapy for patients with esophageal squamous cell carcinoma, S-1 concurrent intensity-modulated radiotherapy has the same effect and less side effects.

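### The 85% power and the total of 88 fit a test of complete response against a fixed 20%, not the between-arm comparison that is expected to show equal effect

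*Protocol article*

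**What the plan says.** Section 3.6 (Statistical analysis and randomization) states the aim of the sample size and its result in these words: "to exclude a lower limit of confidence interval (CI) of 20% CR, the study requires a total of 88 samples". The other inputs given there are an expected CR rate of 40%, two-sided testing at 5%, 85% power, and 10% dropout per arm, with 1:1 allocation. There is one expected rate and one fixed reference rate. No separate rate per arm, between-arm difference or margin is given. The analysis named there for response is a proportion with its 95% CI.

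The purpose stated elsewhere is comparative. The Introduction says the trial was designed "to compare the efficacy and toxicity of combining S-1 or S-1 plus cisplatin with intensity modulated radiation therapy". Section 4 (Discussion) says the experiment was designed to compare the CR rates of the two regimens, and under Expectations that "S-1 concurrent intensity-modulated radiotherapy has the same effect and less side effects". The Discussion paragraph of the Abstract builds its conclusion on the same premise: "If the result will be the same effect and fewer side effects and less costly in S-1 plus radiotherapy".

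**The concern.** The sample size and the intended conclusion answer different questions. The sample size asks whether a CR rate clears 20%. The conclusion asks whether S-1 alone does as well as S-1 plus cisplatin. A reader of section 3.6 will naturally take 85% as the power of the randomised comparison, because that is what the article says the trial is for. If the result is then summarised as equal efficacy with less toxicity, the claim would rest on a comparison for which no margin was set and whose precision is poor. This concerns the primary endpoint and the main conclusion of the trial.

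**Working it through.** **Inputs (section 3.6):** expected CR p1 = 0.40; fixed reference p0 = 0.20; two-sided 0.05; power 85%; dropout 10% per group; total 88, so 44 per arm and 44 × 0.9 = 39.6, about 39–40 evaluable. Normal quantiles: 1.960 (two-sided 5%), 1.645 (one-sided 5%), 1.036 (85% power).

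**1. Reproducing 88 as a one-sample test.** n = (z_a·√(p0·q0) + z_b·√(p1·q1))² / (p1 − p0)².
- Two-sided 5%, plain: (1.960·0.400 + 1.036·0.490)² / 0.04 = 41.7 → 42; 42/0.9 → 47; two arms = 94.
- Two-sided, exact binomial (0.025 per tail): 45 → 50 → 100.
- One-sided 5%, plain: 33.97. With continuity correction, (33.97/4)·(1 + √(1 + 2/(33.97·0.20)))² = 38.8 → 39; 39/0.9 → 44; two arms = **88**.
- Two-sided 95% Wilson interval, 39 evaluable: the lower limit first exceeds 20% at 13 responders (20.6%), and P(X ≥ 13 | 39, 0.40) = 84.5%, close to the stated 85%.

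So 88 = 2 × 44 from a one-sample design, but only with one of the last two variants.

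**2. Trying 88 as a two-arm comparison, 40% v 20%.** n = (1.960·√(2·0.30·0.70) + 1.036·√(0.24 + 0.16))² / 0.20² = 92.7 → 93 per arm, 186 evaluable; 93/0.9 → 104 per arm, 208 randomised. This does not give 88.

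**3. Power of the comparison at the planned size.** Exact enumeration of the two-sided 5% chi-square test, 40% v 20%: 49.7% with 40 per arm, 55.2% with 44.

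**4. Precision if both arms are truly 40%.** Half-width of the 95% CI for the difference = 1.96·√(2·0.40·0.60/n): 0.215 with n = 40, 0.205 with n = 44. That is the whole distance from the expected 40% to the 20% to be excluded.

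**5. Power to exclude a margin under true equality.** The document gives no margin, so 10, 15 and 20 points are assumed. Power = Φ(margin/SE − 1.96), with SE = √(0.48/n).

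| Margin | n = 40 (SE 0.1095) | n = 44 (SE 0.1044) |
|---|---|---|
| 10 points | 15% | 16% |
| 15 points | 28% | 30% |
| 20 points | 45% | 48% |

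**6. What the 20% criterion would catch if applied to the S-1 arm** (control truly 40%, 40 per arm). The lower 95% limit exceeds 20% from 14 responders (exact) or 13 (Wilson).
- S-1 truly 20%: a non-significant chi-square together with an S-1 lower limit above 20% occurs in 1.9% (exact) or 4.2% (Wilson) of trials.
- S-1 truly 30%: P(X ≥ 14 | 40, 0.30) = 30% and P(X ≥ 13 | 40, 0.30) = 42%, so the S-1 arm would clear the benchmark in roughly a third of trials. Power of the comparison is Φ((0.10·√40 − 1.960·√(2·0.35·0.65)) / √(0.24 + 0.21)) = Φ(−1.03) = 15%.

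**7. Power of the benchmark itself at true 40%.** Exact interval: 75% with 39 evaluable, 79% with 40, 83% with all 44. Wilson: 84.5%, 87% and 83%.

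**The case against.** A randomised phase II trial may properly size each arm against a benchmark, with randomisation serving to give comparable estimates. The statement of equal effect is labelled as an expectation in section 4 and is conditional in the Abstract. Section 3.4 says a final statistical plan will follow, and it may specify how CR is compared. All of this stands: the benchmark design is not at fault, and the absence of a named between-arm CR test is not a finding. What remains is a conflict on the page. Section 3.6 fixes the basis of the sample size, and section 4 says the experiment was designed to compare CR rates.

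A reader might infer more than the document supports:
- **That S-1 could halve CR and still be declared equal about half the time.** This ignores the 20% lower limit. If it is applied to the S-1 arm, the joint event occurs in about 2–4% of trials.
- **That a non-significant test or overlapping intervals will be reported as equal efficacy.** No such rule for CR is written. It is a risk to close off, not a stated plan.
- **That the document says the 85% applies to each arm.** Only the dropout is given per group. The per-arm reading is inferred from 88 = 2 × 44.

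It could also be argued that 88 comes from a non-inferiority design: (1.645 + 1.036)²·0.48/0.30² = 38.3 → 39 → 44 → 88, with a 30-point margin at one-sided 5%. But no margin is stated, the test is described as two-sided, and a fall in CR from 40% to 10% would sit at that margin. The match is a coincidence.

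**Conclusion.** The concern holds in a limited form. The stated 85% is not a property of the comparison that the article says the trial was designed to make. For 40% v 20% that comparison has about 50–55% power, and under equality its 95% CI spans about ±21 points, so a conclusion of equal effect cannot be supported at this size. A 20-point loss would usually be caught by the lower-limit criterion if it governs the S-1 arm. A loss such as 40% to 30% would often go undetected.

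These figures assume a control CR of 40%, 40 to 44 evaluable patients per arm, and a two-sided 5% chi-square test for the comparison. The power to exclude a margin also rests on assumed margins of 10 to 20 points. A secondary point is that 88 does not follow from the declared two-sided 0.05 by the plain formula (94) or the exact method (100). With an exact interval the benchmark has 75–83% power rather than 85%.

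**What to change.** Do not enrol more patients; change the wording before analysis.

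1. In section 3.6, state that the 85% refers to each arm's CR rate against 20%. Name the interval method and give the power it provides at two-sided 0.05 with the expected number evaluable. State that the between-arm comparison has about 50–55% power for 40% v 20%.
2. Report the difference in CR rate (S-1 minus S-1 plus cisplatin) with its 95% CI, as an estimate.
3. Replace the equal-effect conclusion with whether the S-1 arm's lower 95% limit exceeds 20%. State that similar efficacy will not be inferred from a non-significant test or from overlapping intervals, but only if the CI of the difference excludes a margin fixed before analysis. Acknowledge that power for this is only about 15–48% for margins of 10 to 20 points.

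Weighting the difference by clinical stage is optional and not part of the correction.

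The cost is protocol and analysis-plan text and a more modest conclusion. Sizing the trial for the similarity claim instead would need, per arm, (1.960 + 1.036)²·0.48/margin² = 431, 192 or 108 evaluable for margins of 10, 15 or 20 points. After 10% dropout that is 958, 428 or 240 randomised in total.

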### Assessment of the primary and secondary endpoints

3.5

In this trial, endoscopic complete response (CR) 3 months after completion of treatment will be evaluated as the primary endpoint. Endoscopic CR was defined as the complete disappearance of any tumor ulceration or stenosis with no new lesion (all endoscopic pictures and reports had to be available), observation of the entire esophagus as defined by Tahara et al,^[22]^ but also no CT-scan progression. Biopsies were not mandatory. Tumor responses were assessed during week 15 according to RECIST guidelines.^[23]^ The primary tumor was assessed on CT scan with measure of the vertical length and maximal thickness of the esophageal wall on transverse plane. Secondary endpoints are the toxicity, progression-free survival (PFS), and overall survival (OS). Adverse events will be encoded in accordance with the requirements of Med DRA. Severity of adverse events will be graded according to the NCI-CTC classification criteria. The toxicity of the treatment, including acute and chronic toxicity will continue to be evaluated during treatment and during follow-up (Table 1). Any serious adverse drug reactions will be reported promptly to the hospital ethics committee. An intent-to-treat analysis (on all randomized patients) was planned for all other end points. PFS was defined as the date from randomization to tumor progression or death. OS was measured from date of study entry to date of death.

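### Read literally, section 3.6 tests progression by chi-square although PFS is a time to event, and gives toxicity no between-arm comparison

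*Protocol article*

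**What the plan says.** The protocol article makes PFS, OS and toxicity secondary endpoints (sections 2.2 and 3.5). On PFS, section 3.5 says: "PFS was defined as the date from randomization to tumor progression or death". It grades the severity of adverse events by the NCI-CTC criteria.

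Section 3.6 assigns the methods: "The Chi-square test and Kaplan–Meier method will be used to analyze the rates and severity of disease progression and overall survival rate, respectively". The sentence then attaches NCI-CTCAE version 4 to these quantities and continues: "a Fisher exact (probability) test will be used to analyze the correlations between clinical outcomes and toxicity". No other method for progression, PFS or toxicity appears in the article.

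The trial means to conclude on toxicity. The Discussion part of the abstract frames the result as "If the result will be the same effect and fewer side effects and less costly in S-1 plus radiotherapy", and section 4 gives the expectation that "S-1 concurrent intensity-modulated radiotherapy has the same effect and less side effects".

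**The concern.** The word *respectively* ties chi-square to progression and Kaplan–Meier to OS alone. A table of progressed against not progressed ignores how long each patient was watched. If one arm is watched for less time, fewer of its progressions are seen and it looks better than it is.

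On toxicity, a Fisher test of outcome against toxicity asks whether patients with toxicity fare differently. It does not ask whether S-1 alone causes less toxicity than S-1 plus cisplatin, which is half of what the trial hopes to report.

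The stake is the analysis of two secondary endpoints. The primary endpoint, endoscopic complete response, is untouched.

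**Working it through.** **Setting the sections side by side**

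| Item | Endpoint or aim | Method stated in 3.6 | Fit |
|---|---|---|---|
| Progression / PFS | time from randomization to progression or death (3.5) | chi-square | no |
| OS | time to death (3.5) | Kaplan–Meier | yes |
| CTCAE grading | adverse events (3.5) | attached to progression and survival | no |
| Toxicity | fewer side effects with S-1 alone (abstract, 4) | Fisher test against clinical outcome | no comparison of arms |

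The plan gives no figure for this point to reproduce. What follows sizes the chi-square problem.

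**Inputs from the article.** 88 patients randomized 1:1, so 44 per arm; recruitment over 1.5 years, so 18 months; planned dropout 10% per group; two-sided 5% level.

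**Assumed inputs, not in the article.** Exponential PFS with median 12 months in both arms; minimum follow-up 12 months, so follow-up uniform from 12 to 30 months; exponential loss to follow-up.

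**Formulas.** Let λ = ln 2 / 12 = 0.0578 per month, δ the monthly loss rate and s = λ + δ.

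- Q = 1 − (e^(−12s) − e^(−30s)) / (18s)
- Proportion with an observed event: p = (λ/s) × Q
- Proportion lost before an event: (δ/s) × Q
- Chi-square rejection rate, approximately: Φ(z − 1.96) + Φ(−z − 1.96), where z = |p₁ − p₂| / √{[p₁(1 − p₁) + p₂(1 − p₂)] / 44}

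**Results with no true difference**

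| Lost, control / S-1 | δ, control / S-1 | Observed events, control / S-1 | z | Chi-square rejects |
|---|---|---|---|---|
| 10% / 10% | 0.0090 / 0.0090 | 63.9% / 63.9% | 0 | 5% |
| 15% / 5% | 0.0141 / 0.0043 | 61.3% / 66.4% | 0.50 | 8% |
| 28% / 11% | 0.03 / 0.01 | 54.3% / 63.4% | 0.87 | 14% |

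For the last row, the difference is 0.634 − 0.543 = 0.091 and the standard error 0.1045, so z = 0.87 and Φ(−1.09) + Φ(−2.83) = 0.14. Simulation of whole trials agrees, with log-rank near 5% in every row. The error here favours the arm with more loss. An extreme case of 46% against 11% lost gives about 44% by simulation.

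**Power, no loss.** With medians of 12 and 20 months, the observed event proportions are 68.9% and 50.9%. Then z = 0.180 / 0.1027 = 1.75 and power is Φ(−0.21) = 42%. Log-rank has 46% by simulation.

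**Sensitivity to the assumed follow-up (simulation).** With annual loss of 20% against 5%, the chi-square false-positive rate is 12% at a 12-month minimum follow-up and 24% at 24 months; with 30% against 5% it is 21% and 50%. Log-rank stays at 5.4% to 5.8%. With equal follow-up and a hazard ratio of 0.5, power for chi-square against log-rank is 53% against 58% at a 6-month minimum, and 71% against 84% at 36 months.

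**The case against.** The strongest reply is that the sentence is corrupt and should not be read literally. Severity and CTCAE grade belong to adverse events. A natural repair is chi-square for toxicity rates and severity, with Kaplan–Meier for progression and OS, which would supply both missing analyses. This is plausible, and it means one cannot say that PFS *will* be tested by chi-square. It does not remove the need for correction: the text does not say it, and *respectively* gives the other pairing.

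Second, section 3.4 refers to a final statistical plan, and details such as the log-rank test or a Cox model are commonly left there. Their absence alone would be no finding. The finding is that the methods the article does state do not fit its endpoints.

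Third, the large false-positive rates need loss well beyond the planned 10% per group and unequal between arms. That stands. Section 3.1.3 makes a toxicity delay of more than two weeks a drop-out criterion, and more toxicity is expected with two drugs, so unequal loss is possible. But section 3.5 plans intent-to-treat for the other endpoints, so stopping treatment need not end follow-up.

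A reader might also infer three further faults that the article does not support:

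- **Staggered entry alone biases the comparison.** Randomization balances entry time. With no loss, simulation gave 5.5% for chi-square and 5.2% for log-rank.
- **PFS and OS have different time zeros.** Section 3.5 says "OS was measured from date of study entry to date of death", but no registration step or run-in before randomization is described, so the two dates may be the same. This is tidying.
- **The outcome–toxicity correlation is distorted because longer survivors have more time to show toxicity.** That assumes the outcome is survival. Section 3.6 does not define it, and it could be response, assessed at about three months.

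**Conclusion.** Section 3.6 is wrong as written, for secondary endpoints only. Taken literally, it gives PFS a test that ignores follow-up time and gives toxicity no comparison of the arms, although the trial intends to conclude on both similar effect and fewer side effects. The likeliest cause is garbled drafting.

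The toxicity gap needs no numerical assumption. The harm to PFS depends on loss: a small loss of power and no inflation at about 10% lost in each arm, about 8% false positives at 15% against 5%, and about 14% at 28% against 11%. These figures rest on an assumed 12-month median PFS and 12-month minimum follow-up, and grow with longer follow-up. The article does not support a claim that PFS results will be materially biased; that requires loss that differs by arm, beyond what is planned.

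**What to change.** Rewrite the sentence in section 3.6, before the data are locked, so that:

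1. PFS and OS, both measured from randomization, are analysed by Kaplan–Meier with a log-rank test and a hazard ratio with 95% CI.
2. CTCAE version 4 toxicity, for example the proportion with any grade 3 or higher event, is compared between arms by chi-square or Fisher exact test, with the difference and its 95% CI. The interval matters: at 44 per arm, power is about 54% for assumed rates of 40% against 20%.
3. The correlation of clinical outcome with toxicity is kept as exploratory.

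The cost is wording. The same data are used, and neither the sample size nor the primary analysis changes.

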### Ethics

3.7

The trial received ethical approval from the Ethics Committee of Mianyang Central Hospital, Sichuan, China (number: S2016055). The trial is subject to the supervision and management of the ethics committee.

### Trial status

3.8

This study opened to recruitment in October 2016, with a planned recruitment period of 1.5 years.

## Discussion

4

CRT has been accepted nowadays as the standard nonsurgical treatment for locally advanced EC.^[24]^ For 2 decades, chemotherapy, especially the 2-drug combination of cisplatin plus fluorouracil has been regarded as a standard regimen to treat patients with EC with distant metastases or recurrence.^[25]^ However, some retrospective studies have suggested that for patients with EC receiving radiotherapy combined with 2-drug chemotherapy have the severe toxicity.^[7,13–17]^ Our retrospective analysis of 133 cases of esophageal squamous cell carcinoma with complete statistical data found that for both OS and PFS, there was no significant difference between single and 2-drug chemotherapy combined with synchronous radiotherapy (unpublished). So we design this experiment to compare the complete remission rate of S-1 and S-1 combined with cisplatin in the treatment of esophageal squamous cell carcinoma.

*Expectations*: Compare S-1 plus cisplatin concurrent intensity-modulated radiotherapy for patients with esophageal squamous cell carcinoma, S-1 concurrent intensity-modulated radiotherapy has the same effect and less side effects.
